**Table 3 T3:**

Frankl behavior rating scale.

**Table 4 T4:**

Parent's dental treatment acceptance questionnaire.

**Table 5 T5:**
[figure not shown]
Children's dental treatment acceptance questionnaire.

### Sample size calculation

2.3

The size of the sample necessary to detect a statistically significant difference was determined with a power calculation based on the results from studies carried out using the same outcome measures to evaluate behavior.^[19]^ To achieve an 80% power to detect a difference between the two groups a sample size of 30 patients was required. To compensate for dropout rate of 20% to 30%, that is, we decide to recruit 40 children in each group.

### Patient and public involvement

2.4

#### Development of the research question and outcome measures informed by patients’ priorities, experience, and preferences

2.4.1

A survey on the preference for the use of a familiarization to IHS before commencement of treatment was carried out involving 15 children, aged 5–15 years. The results were inconclusive with eight out of 15 children expressing preference for starting treatment without familiarization to sedation. This formed our primary outcome measure on comparing changes in self-reported anxiety scale in children who have familiarization visit and those who do not.

#### Involvement of patients in the design of this study

2.4.2

As part of the above survey, we also asked children how they would feel completing MCDASf (anxiety form) and, we explained to them and demonstrated the process of collecting the salivary sample. 12 out 15 children were happy with the salivary sample collection method, three children found it uncomfortable. All the children in this survey mentioned that completing MCDASf was fine.

#### Involvement of patients in the recruitment to and conduct of the study

2.4.3

The patients who will be recruited in this study will already be indicated for treatment under IHS in any case.

#### Study results dissemination

2.4.4

We will have a dissemination event inviting participants/guardians, dental teams including general dental practitioners, dental nurses, specialists, and consultant to discuss our findings as it will be of interest to all those who manage children with dental anxiety. The results of the study will be presented at national and international conferences and will be submitted to a high impact factor dental journal.

#### Assessment of the burden of the intervention the participants

2.4.5

We discussed the randomization with the children in the survey and 10 out of 15 children were happy to be randomized and were not overly concerned with whichever arm they would be randomized to. For children younger than 10 years, the opinion of the parents/guardians will be sought.

### Ethical considerations and dissemination

2.5

All parents/caregivers and children fulfilling the inclusion criteria will be eligible for participation. In addition, to a routine verbal and written information and treatment consent form signed by parent/caregiver of the child before treatment under IHS, participating children's parents/caregivers will be informed verbally and in writing about the study. Participants and their parents/guardians will be appropriately informed about the objectives of the study; each participant will be ensured anonymity. Participants and their legal guardians will be informed about their right to withdraw from the study at any point. Appendix 1, http://links.lww.com/MD/D198 includes the consent forms both in English and Arabic. Following data analysis, collective results will be published. A signed, informed consent form will be required for participation from the parents/caregivers. The study has been approved by the ethics and research committee of Mohammed Bin Rashid University of Medicine and Health Sciences (Reference: MBRU-IRB-2018-014).

The results of the study will be disseminated through peer-reviewed publication/s, conference presentations, and the University web site. We will also have a dissemination event inviting dental teams including general dental practitioners, dental nurses, specialists, and consultant to discuss our findings as it will be of interest to all those who manage children with dental anxiety. Alongside these traditional outputs, our Forum, will help produce a simple and short end of trial English summary. This will be outreached to the wider community.

### Data management and statement

2.6

Each participant will be assigned a unique study code number. Participant identifiers which will be collected will include name, phone number and clinic file number. Clinical recording sheets, Alpha Amylase and Cortisol immunoassay data will only be labelled using the code number.

### Data management committee

2.7

This will comprise of the PI [name], administrative staff and the study biostatistician. This team will be responsible for data entry and verification as well as ensuring that the collected data is stored securely. The list connecting the participant name/contact details with the study code number will be kept in a locked cabinet in the principal investigator's office. Only the principal investigator will have access to this list.

Anonymous participants’ data may be shared on request to promote culture of openness and an increased sharing of research data. Our information sheet and informed consent clearly state that the collected data are intended to be used for research purposes, and possibly published in dental journals and presented at conferences. All the anonymously collected data can be shared upon request from the primary investigator once the study is completed. The data will be stored for five years after the final publication to be shared upon request.

### Statistical analysis

2.8

Data analysis will be conducted, after investigating distribution normality, with the appropriate parametric or non-parametric statistical tests using the statistical software SPSS 24.0.0 (^©^SPSS Inc, Chicago, Ill). The level of significance will be set at *P* < .05. Use of Descriptive statistics and quantitative data will be analyzed using means and standard deviations if normally distributed or medians and interquartile range if skewed. Mean changes of anxiety scores and corresponding 95% confidence intervals will be determined to compare the two treatments (sedation with familiarization and sedation without familiarization). *T*-tests will be used to compare quantitative data if normally distributed or Mann–Whitney *U*-test if skewed. The Chi-square test will be used to investigate association of categorical data. Box plots, individual and mean profiles of anxiety scores at each assessment time point for each treatment will be produced.

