### Primary outcome

2.1

Improvement in behavior and anxiety levels. The primary outcome measured by:

(1)Physiologically by measuring anxiety-related changes using salivary levels of Alpha Amylase and Cortisol.(2)Anxiety scores at baseline (initial visit) and after treatment (second visit) using a component from the indicator of sedation need (IOSN).(3)Behavior score will be recorded using, Frankl behavior rating scale (FBRS).

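### The arms are compared without baseline adjustment, by a test picked after looking at the data, although visit-1 anxiety and saliva values are collected; a prespecified ANCOVA would be more precise

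*Protocol article*

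**What the plan says.** Statistical analysis (2.8) gives the between-arm comparison for anxiety as follows: "Mean changes of anxiety scores and corresponding 95% confidence intervals will be determined to compare the two treatments". Quantitative data generally are to be analysed "with the appropriate parametric or non-parametric statistical tests", once normality has been looked at: a t-test if the data appear normal, Mann–Whitney if skewed. Summaries switch in the same way, from mean and SD to median and interquartile range. On significance it says "The level of significance will be set at *P* < .05". No model with a baseline covariate is mentioned.

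Primary outcome (2.1) lists "Anxiety scores at baseline (initial visit) and after treatment (second visit"), so a baseline anxiety score exists. The procedures text after Figure 1 adds a saliva sample for amylase and cortisol at the start of visit 1, and two more at visit 2: 15 minutes before and 15 minutes after the procedure. The sedation-need index, which contains the anxiety scale, is recorded during visit 1. The Frankl behaviour score has no described baseline measurement.

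**The concern.** In a small randomised trial with a baseline measurement of the outcome, the choice of analysis decides how much of the between-child variation is removed. A change score subtracts the whole baseline value, as if the visits were perfectly related. A comparison of final values ignores baseline. ANCOVA estimates the right amount from the data, so it is more precise than either except at the extremes of the correlation.

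The second issue is that the test is left open until the data have been seen. For anxiety scores this has a concrete effect. The mean-change confidence interval is promised unconditionally, but under skew the P value would come from Mann–Whitney, which tests something other than a difference in means. The two can disagree, and the plan does not say which one carries the conclusion.

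At stake are precision and a clear primary estimate, not the validity of the trial.

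**Working it through.** **Inputs from the document.** Significance level 0.05 (sidedness not stated; two-sided assumed). Allocation 1:1. Sample size calculation (2.3): "To achieve an 80% power to detect a difference between the two groups a sample size of 30 patients was required", read as per group because the same section goes on: "we decide to recruit 40 children in each group".

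**Inputs the document does not give.** The effect size, the SD and the test behind the calculation, which is only described as "based on the results from studies carried out using the same outcome measures to evaluate behavior"; and the correlation r between visit-1 and visit-2 values. I assume r = 0.3, 0.5 and 0.7, and equal SDs at both visits.

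**Plan's own figure.** The 30 cannot be reproduced without an effect size. Solved backwards (two-sample t-test, 30 per arm, 80% power), it implies a standardised difference d = 0.736. The step to 40 can be checked: 30/(1−0.20) = 37.5, rounded up to 38; 30/(1−0.25) = 40; 30/(1−0.30) = 42.9, rounded up to 43. So 40 recruited per arm leaves 30 at 25% dropout, and 30 per arm is a fair analysed size.

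**Variances, in units of SD².** Final value: 1. Change: 2(1−r). ANCOVA: 1−r². Hence ANCOVA/change = (1−r²)/[2(1−r)] = (1+r)/2.

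**Power.** Noncentral t with noncentrality (d/√v)·√(n/2), where v is the variance factor, with 58 df for the t-test and 57 for ANCOVA. With d = 0.736, v = 1 and n = 30 this is 0.736 × √15 = 2.85, which gives 80%.

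*Anchor A: 30 per arm gives 80% on change scores.* Divide 2.85 by √((1+r)/2).

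| r | ANCOVA/change variance | Noncentrality | ANCOVA power | ANCOVA n per arm for about 80% |
|---|---|---|---|---|
| 0.3 | 0.65 | 3.53 | 93.5% | 30 × 0.65 = 19.5, so 20 |
| 0.5 | 0.75 | 3.29 | 89.9% | 30 × 0.75 = 22.5, so 23 |
| 0.7 | 0.85 | 3.09 | 85.9% | 30 × 0.85 = 25.5, so 26 |

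*Anchor B: 30 per arm gives 80% on the final value.* Divide 2.85 by √(2(1−r)) for change and by √(1−r²) for ANCOVA.

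| r | Final value | Change | ANCOVA |
|---|---|---|---|
| 0.3 | 80.0% | 65.8% | 83.5% |
| 0.5 | 80.0% | 80.0% | 89.9% |
| 0.7 | 80.0% | 95.1% | 97.5% |

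**Simulation check.** 3,000 runs per setting, normal data, 30 per arm, d = 0.74. The planned two-stage choice on change against ANCOVA gave 66% v 83%, 80% v 89% and 96% v 98% at the three correlations, in line with anchor B.

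**Cost of the covariate.** In the worst case against a final-value test (r = 0), allowing for the lost degree of freedom and the variance factor 1 + 1/56, power falls from 80.0% to 79.3%. Against change scores, ANCOVA loses only when r is close to 1: 79.7% against 80.0% at r = 0.98.

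**Type I error.** In simulations with no effect, including skewed data, every method stayed between 4.5% and 5.7%, the two-stage choice among them.

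**The case against.** The best reply is that this is a preference about efficiency. Under 1:1 randomisation an unadjusted comparison is unbiased, and covariates and transformations are commonly left to a statistical analysis plan, which is not shown here. The first half stands. The second does not remove the point: the article names the tests and the change-score comparison, so a later plan using ANCOVA would depart from the published text.

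Several stronger readings are tempting and are not supported:

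- *All outcomes are compared on changes.* The text says this only for anxiety scores. For amylase and cortisol it refers only to quantitative data, so change or final value is open. Either would be unadjusted, but the (1+r)/2 ratio applies only if change is meant.
- *The normality check inflates false positives.* The simulations show no such effect. The text also names no formal normality test.
- *P value and interval clash for every outcome.* A mean-change interval is promised only for anxiety scores; elsewhere the summaries switch with the distribution.
- *The trial has 80% power on change scores and would have 93.5% with ANCOVA.* The sample size section names no test, effect or SD. Under anchor B at r = 0.7 the gain over change scores is only 97.5 − 95.1 = 2.4 points.
- *Chance imbalance makes the planned analysis biased.* It costs precision; it does not invalidate the test.

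**Conclusion.** The point holds as one of efficiency and prespecification. The plan fixes unadjusted comparisons while usable visit-1 values of the anxiety score and both saliva markers are collected, and it leaves the choice of test to the data. For anxiety scores under skew, the P value would not correspond to the promised interval.

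The direction of the gain is secure unless r is near 0 (against final values) or near 1 (against change). Its size is illustrative, because it rests on equal SDs, an assumed r of 0.3 to 0.7 and an assumed anchor for the 80%. For anxiety it is 5.9 to 13.5 power points over change scores under anchor A (85.9 − 80.0 to 93.5 − 80.0), and 2.4 to 17.7 under anchor B (97.5 − 95.1 to 83.5 − 65.8). I claim no figure for amylase or cortisol. The Frankl score is outside the point. The change should be made, but the planned analysis is not invalid without it.

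**What to change.** In Statistical analysis, replace the data-chosen test with one prespecified ANCOVA for the anxiety score and one for each saliva marker:

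- Outcome: the visit-2 value. For saliva, state which sample is meant: the post-procedure one, or each of the two in its own model.
- Covariate: the visit-1 value of the same measure. The visit-2 pre-procedure sample is taken after the intervention and must never serve as baseline.
- Scale: the anxiety score as recorded; amylase and cortisol on the log scale, decided in advance.
- Report: the adjusted difference, or for the markers the adjusted ratio, with 95% CI. Keep Mann–Whitney as a sensitivity analysis and drop the normality check as the selector.
- Age and treatment complexity are optional covariates; no gain from them has been shown here.

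Also confirm in the text that the visit-1 anxiety score is taken before nitrous oxide. The procedures place the saliva sample at the start of that visit but do not give the order for the score. Leave the Frankl score out of this change unless a baseline is recorded.

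The cost is a change of wording and one degree of freedom per model. No further data are needed, and the named SPSS software can fit the model.

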**Figure 1 F1:**
[figure not shown]
Flowchart of the study design.

After baseline examination by the clinical team, eligibility verification, the primary investigator will obtain the participant's assent and parents’/guardian's consent submission (Appendix I, http://links.lww.com/MD/D198), participants will be randomized to either of the two study groups (30 patients per group). The study group will include families (children and parents) who would attend a visit for prevention where IHS will be introduced and tried while the control group will be the families who would attend for a prevention visit and discussion of IHS procedure only.

Block randomization with a 1:1 allocation will be performed. Concealment of allocation will be achieved by using identical, sealed, sequentially numbered, opaque envelopes that will contain group assignment. The envelopes will be opened sequentially by a dental assistant, only after the envelope has been irreversibly assigned to each participant and will remain unknown to the clinical team.

At the initial acclimatization visit, the sedation need score will be recorded using the pediatric indicator of sedation need (p-IOSN). Acclimatization visit will be carried out by a single pediatric dentist who will not be involved in the treatment of the patients. To be consistent, an information script will be prepared and rehearsed so that the same instructions about the IHS will be delivered to all participants. During the acclimatization visit, the pediatric dentist will record the p-IOSN score based on the answers of the participants to the components of the index. At the beginning of the visit, an unstimulated salivary sample of 1.5 to 2 ml will be collected to measure the levels of Alpha Amylase and Cortisol. For the intervention group only, a 15 minutes nitrous oxide IHS will be administered without any dental procedures performed.

During the second visit, two unstimulated 1.5 to 2 ml samples of saliva will be collected 15 minutes before the start of the procedure and 15 minutes after the conclusion of the procedure. The dental treatment for both study and control participants will include administering local analgesia and restoring decayed teeth with or without pulp therapy and/or dental extractions. The intervention will be carried out by a single pediatric dentist.

The 3 components of p-IOSN (Fig. 2, Tables 1 and 2) include:

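### Section 2.8 answers skewness only by switching to Mann–Whitney, so skewed amylase and cortisol get a P value without an effect estimate, and possibly lower power if untransformed changes are compared

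*Protocol article*

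**What the plan says.** Section 2.1 (Primary outcome) lists the saliva measure first: "Physiologically by measuring anxiety-related changes using salivary levels of Alpha Amylase and Cortisol". The Methods text after Figure 1 provides three samples per child: one at the start of visit 1, and two at visit 2, before and after the procedure. The article does not say which of these are compared, or whether the quantity tested is a change or a level.

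Section 2.8 (Statistical analysis) has one rule for all continuous data. Normality is examined first, and then t-"tests will be used to compare quantitative data if normally distributed or Mann–Whitney" *U* if skewed. The matching summary is that "quantitative data will be analyzed using means and standard deviations if normally distributed or medians and interquartile range if skewed". The section mentions no transformation and does not name amylase or cortisol. Its only between-arm comparison with a 95% confidence interval is for mean changes in anxiety scores.

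**The concern.** Two consequences follow if the markers are right-skewed, which is plausible for concentrations that cannot be negative.

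- **No estimate.** The skewed branch of the rule gives a test and two medians with their spread. It gives no measure of the difference between arms and no interval. Yet the Discussion presents the difference in these two markers as what the trial offers to guideline writers.
- **Scale.** For a single level, Mann–Whitney is unaffected by taking logs, so the rule costs little. A change is different. The raw difference between two right-skewed values is not a monotone function of their log ratio. A child with a high level and a small proportional fall can outrank a child with a low level whose value halves. Moving to ranks after the subtraction does not undo this, so a real proportional effect may be missed.

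**Working it through.** **Inputs from the article.** For alpha, "The level of significance will be set at" 0.05; I take it as two-sided. Power and size: "To achieve an 80% power to detect a difference between the two groups a sample size of 30 patients was required". The Methods text makes that 30 per group ("participants will be randomized to either of the two study groups (30 patients per group"), and "Block randomization with a 1:1 allocation will be performed". Section 2.3 recruits more: "To compensate for dropout rate of 20% to 30%, that is, we decide to recruit 40 children in each group". With 20% to 30% dropout, 40 leaves 40 × 0.8 = 32 to 40 × 0.7 = 28 children per arm, so 30 is a fair analysable number.

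**The plan's own figure.** The 30 cannot be reproduced, because no effect size, SD or test is given. Back-solved with the normal approximation, d = (1.96 + 0.84) × √(2/30) = 2.80 × 0.258 = 0.72; with the t distribution it is 0.736. The 40 matches 25% dropout: 30 / 0.75 = 40.

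**Assumptions not in the article.** Markers lognormal; log-SD *s* from 0.2 to 1.1; within-child log correlation ρ from 0.3 to 0.85; effect proportional. The effect is set so that a t-test on log ratios has 80% power: log effect = 0.736 × *s* × √(2(1 − ρ)). For *s* = 0.5 and ρ = 0.5 this is 0.368, a ratio of exp(−0.368) = 0.69.

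**Simulated power, 30 per arm, ρ = 0.5** (8,000 to 10,000 trials per setting; 3,000 for the rule, taken as a Shapiro–Wilk check followed by the t-test or Mann–Whitney on raw change):

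| log-SD | t, log ratio | t, raw change | Mann–Whitney, raw change | Rule | Mann–Whitney, log ratio |
|---|---|---|---|---|---|
| 0.2 | 80% | 76% | 74% | 75% | 78% |
| 0.3 | 80% | 72% | 71% | 73% | 78% |
| 0.5 | 80% | 64% | 66% | 66% | 78% |
| 0.7 | 80% | 53% | 62% | 61% | 78% |
| 0.9 | 80% | 43% | 58% | 57% | 77% |
| 1.1 | 80% | 35% | 55% | 53% | 78% |

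Across the correlations, Mann–Whitney on raw change has 66–69% at log-SD 0.5, 61–65% at 0.7, 58–62% at 0.9 and 55–57% at 1.1. The rule as a whole stays within 1 to 2 points of it. The simulation standard error at 3,000 trials is about √(0.6 × 0.4 / 3000) = 0.9 points. Type I error was about 4 to 5% for the tests on change. With 40 per arm, and the effect re-sized to 80% power, the rule still loses from 80.0 − 67.8 = 12 points (log-SD 0.5) to 79.4 − 56.5 = 23 points (log-SD 1.1).

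**Where the loss is small or reverses.**

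- *Low skewness.* At log-SD 0.3 the loss is about 5 to 9 points.
- *Levels instead of changes.* At ρ = 0.5 the log change has variance 2(1 − 0.5)*s*² = *s*², the same as a log level, so a t-test on log levels also has 80%. Mann–Whitney on levels has about 77.5%, a gap of 2 to 3 points.
- *Additive change with constant noise.* The raw t-test has about 80% and raw Mann–Whitney 77%. The log-ratio t-test has 71–76% in one set of runs and about 49–75% in another.

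**Adjusting for baseline.** On the log scale, adjustment reduces the variance from 2(1 − ρ)*s*² to (1 − ρ²)*s*², a factor of (1 + ρ)/2 = 0.75 at ρ = 0.5. Simulated power for the adjusted log analysis is 85–93% for ρ from 0.3 to 0.7. At ρ = 0.5, adjustment on the raw scale against the log scale gives 84% against 89% at log-SD 0.5, and 72% against 91% at log-SD 0.9. Adjustment alone does not remove the scale problem.

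**The case against.** The strongest reply is that Section 2.8 is a general and valid rule. It never commits the saliva markers to a raw-scale analysis and does not exclude transformation. The wording of Section 2.1 can mean physiological changes that accompany anxiety rather than change scores, and the aim and hypothesis speak of levels. The choice of transformation and of an estimator to go with a rank test often sits in a statistical analysis plan, and one may exist unseen. Type I error is held.

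Much of this stands. A reader might infer that the plan fixes a raw-change analysis that costs a known number of power points. The documents do not support that: they give no salivary SD, correlation, distribution or effect form, and they do not settle change against level. A reader might also infer that the plan gives no effect estimates at all, but intervals are planned for anxiety scores. Nor is the log scale always better, as the additive case shows.

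What does not stand is that this is mere silence. Section 2.8 states how skewed continuous data will be tested and summarised, and for two primary measures that stated method leaves the size of the effect unreported.

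**Conclusion.** The point holds in a conditional form. The missing estimate needs no distributional model: whenever amylase or cortisol is judged skewed, the stated rule gives a P value and medians, with no between-arm effect size or interval. The normality check, run on the trial data, also decides which summary is reported.

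The power loss is an if-then statement. Comparing untransformed within-child changes is the natural but not explicit reading of Section 2.1. If that is done, with lognormal markers at log-SD 0.5 to 1.1 and a proportional effect, power at 30 per arm is about 55 to 68% against 80% for a log-ratio t-test. Outside those assumptions the loss is minor, or the log ratio is the weaker choice. This is a matter of efficiency and reporting, not of validity. I would ask for the change because it is cheap, with medium confidence in the size of the gain.

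**What to change.** In Section 2.8, prespecify that amylase and cortisol are log-transformed. Compare the arms on the log visit-2 value adjusted for the log value from the sample already taken at visit 1, and name which of the two visit-2 samples is used. Report the ratio of geometric means with its 95% confidence interval, and keep the Mann–Whitney test as a sensitivity analysis.

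The cost is a sentence or two of wording and no new data. Results are then read as ratios, values below the assay limit need a substitute fixed in advance, and power may be lost if the true effect is additive.
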